### Sample size

Sample size is based on studies included in our systematic review [7]. In a single study investigating a similar contrast of interventions [9] there was an absolute increase in recovery of 22% (19% recovery in the usual care group to 41% recovery in the exercise therapy group) after one year, OR 2.21 (95%CI 0.87 – 5.64)). This represents a clinically relevant increase and is expected to be even more pronounced after 3 months follow-up. Such a difference can be detected statistically (power 0.80, alpha 0.05 one-sided test) with 61 patients per group. With a potential dropout rate of 10% a total of 136 patients should be included.

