### Measurements

#### Outcome parameters

Primary outcome measures are: perceived recovery (measured with a 7 point Likert scale [10] functional disability using a disease-specific disability scale (Kujala Patellofemoral Scale) [11] and a pain severity using a numerical rating scale[12] after 3 and 12 months of follow-up. (Table 1)

Secondary outcome measures are cost-effectiveness after one year, the primary outcome parameters at 6 weeks follow-up, quality of life (Euroqol)[13] and a numerical rating scale (NRS 0–10) for difficulties encountered during work, school or sports activities. Medical consumption (visits to health care providers and consumptions of prescription or over the counter medication), absence from work or decreased productivity at work, and other indirect an direct costs are all included in the economic evaluation.

Baseline and follow-up questionnaires at 6 weeks and 3 and 12 months will be filled out by the patients themselves. Quality of life, direct costs and productivity costs and compliance to the interventions will be measured after 6 weeks and every 3 months during one year also by self report.

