### Analyses

All analyses will take place after the trial has finished, no intermediate analyses will be performed.

To evaluate the effectiveness of supervised exercise therapy in patients with PFPS differences in clinical outcome measures between intervention and control group will be analyzed on the basis of intention to treat. Additionally, analysis per protocol will be conducted. Dichotomous outcomes at three and 12 months follow-up will be analyzed using logistic regression techniques and continuous outcomes with linear regression techniques. Of the primary outcomes perceived recovery will be dichotomized to recovered (fully, strongly) or not recovered (slightly-strongly worsened). Other primary outcome measurements will be analyzed as continuous variables

Analyses will be adjusted for baseline values and for co-interventions and possible prognostic factors in case the effect estimate changes with more than 10% when including these variables in the model.

Additionally the overall one year dichotomous outcomes will be analyzed using GEE (generalized estimating equations) [14], continuous outcomes will be analyzed using linear regression for repeated measurements. Both techniques take the correlation of multiple measurements within one patient into account.

Research question 2 "What is the cost-effectiveness of supervised exercise therapy in patients with PFPS...." is the basis for the economic evaluation.

In the economic evaluation (a cost utility analysis) both the costs and the consequences of both treatment options are compared and incremental costs and incremental health effects the latter (in terms of quality of life) is estimated.

The economic evaluation is performed alongside the randomized clinical trial. Patients will complete questionnaires for costs and quality of life after 6 weeks and every 3 months. Only if the difference in health between the treatment arms appears not to be stable over time, an additional modeling study using a Markov model will be performed. Statistical methods are used to describe uncertainty in costs and effects estimates based on patient data. A 95% confidence interval for the cost-utility ratio will be calculated and an acceptability curve will be presented

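### The adjustment rule does not define which baseline terms enter the models for perceived recovery, the outcome the trial is sized on

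*Protocol article*

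**What the plan says.** Three parts of the protocol article bear on this.

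- **Sample size.** The trial is sized on recovery, "19% recovery in the usual care group to 41% recovery in the exercise therapy group", with "power 0.80, alpha 0.05 one-sided test) with 61 patients per group". Allowing for dropout, the total is 136.
- **Outcome parameters.** Perceived recovery on a 7-point Likert scale, the Kujala score and a numerical pain rating are the primary outcomes at 3 and 12 months. The schedule is "Baseline and follow-up questionnaires at 6 weeks and 3 and 12 months".
- **Analyses.** The cut on the Likert scale is given as "perceived recovery will be dichotomized to recovered (fully, strongly) or not recovered (slightly-strongly worsened". Recovery at 3 and 12 months goes into logistic regression, and the one-year course into GEE. For all analyses the rule is "Analyses will be adjusted for baseline values". The same sentence adds co-interventions and possible prognostic factors, subject to a change of more than 10% in the effect estimate. It names no baseline variable for any outcome, and its grammar leaves open whether the 10% condition also governs the baseline values.

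**The concern.** The recovery categories run from full recovery to strong worsening. They compare the patient's present state with the start, so they cannot be scored before treatment. For two primary outcomes the rule points to an obvious covariate; for the third, and the one that sets the sample size, it does not. Two analysts following the same sentence could fit different models: no baseline term, baseline pain and Kujala always in, or these scores in only when they move the estimate enough.

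At stake are some power on the sizing outcome, protection against a chance imbalance in severity (the Randomization section stratifies on setting and age only), and a recovery model that is fixed before the data are seen.

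**Working it through.** **1. The plan's own figure.** Inputs from Sample size: 0.19 and 0.41, difference 0.22, mean 0.30, one-sided 5% (z = 1.645), power 80% (z = 0.842).

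- Uncorrected: n = [1.645·√(2·0.30·0.70) + 0.842·√(0.19·0.81 + 0.41·0.59)]² / 0.22² = 52.6, so 53 per group.
- With continuity correction: (52.6/4)·[1 + √(1 + 4/(52.6·0.22))]² = 61.4, which is 62 rounded up, against 61 stated.
- Dropout: 122/0.9 = 135.6, so 136.

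The stated size is reproduced, and it assumes no covariate adjustment. Uncorrected power at 61 per group is 85% one-sided and 76% two-sided.

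**2. Power with baseline severity fixed in the model.** The article gives no prognostic strength, so a range is assumed. Simulation: 8,000 trials per setting, 61 per group, marginal recovery 19% v 41%, two baseline covariates correlated 0.5 that together explain a share R² of latent (logistic) variation.

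| R² | One-sided 5%: unadjusted → adjusted | Two-sided 5%: unadjusted → adjusted |
|---|---|---|
| 0.05 | 85.0 → 86.0% | 76.3 → 77.1% |
| 0.10 | 84.6 → 86.5% | 76.1 → 78.3% |
| 0.20 | 84.4 → 88.6% | 75.8 → 80.8% |
| 0.30 | 86.0 → 91.2% | 77.6 → 84.6% |

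The gains here are 1.0 to 5.2 points one-sided and 0.8 to 7.0 two-sided. Repeat simulations over the same range put the upper end at about 7 and 8 points. A simpler version, with one covariate of odds ratio 1.0 to 2.5 per SD, gives 0 to 5 and 0 to 6 points.

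**3. What the 10% rule does instead.** With the two covariates and R² of 0.05 to 0.30, the change in the odds ratio exceeds 10% in about 34% to 83% of trials. With the single covariate at odds ratio 1.0 / 1.5 / 2.0 / 2.5 per SD, it does so in about 4 / 26 / 54 / 72%.

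Part of this is non-collapsibility, not imbalance. The marginal odds ratio is (0.41/0.59)/(0.19/0.81) = 2.96. With a covariate of odds ratio 2.0 per SD, the conditional odds ratio that gives the same marginal rates is 3.27. The ratio 3.27/2.96 = 1.10 is already at the threshold with perfectly balanced arms.

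**4. Chance imbalance.** A 1-in-20 difference in mean severity is 1.96·√(2/61) = 0.355 SD. With latent covariate SD s = √[R²/(1−R²)·π²/3], the shift on the conditional scale is exp(0.355·s):

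- R² = 0.05: 1.16
- R² = 0.10: 1.24
- R² = 0.20: 1.38
- R² = 0.30: 1.52

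The unadjusted odds ratio itself moves somewhat less, by about 1.2 to 1.45 in simulation for R² of 0.10 to 0.30.

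**5. Can the model carry the covariates?** Expected recoveries are 61·(0.19 + 0.41) = 36.6. With treatment and two covariates that is 36.6/3 = 12.2 recoveries per parameter.

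**The case against.** The strongest reply is that the article speaks of baseline values in general, not of the baseline value of the outcome being analysed. Read broadly, the sentence already allows baseline pain and function in the recovery model. A reader might infer that baseline adjustment is impossible for recovery, or that its models will certainly have no baseline term. The text supports neither: it is ambiguous, not unworkable.

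Second, a covariate list for each outcome is commonly left to a full protocol or SAP, and neither is shown. That is fair, and the absence of a list alone would be no finding. Here, however, the article does state a rule for all analyses, and that rule gives no defined model for one primary outcome.

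Third, the 10% clause offers some protection. In a simulation with one composite covariate explaining 10-30% and a 0.355 SD imbalance, it triggered in about 96-100% of trials when the imbalance went against exercise, but only in about 51-59% when it favoured exercise. The safeguard exists but is uneven, and weakest where the imbalance flatters the intervention.

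Fourth, the unadjusted comparison is valid under randomisation. Chance imbalance is already covered by its error rate and confidence interval, and unadjusted one-sided power of about 85% exceeds the planned 80%. All of this stands and limits the weight of the point.

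Finally, the article's text does not list what is collected at baseline. That pain and Kujala are collected then is inferred from three things: the baseline assessments placed before allocation in Randomization, the baseline questionnaire in Outcome parameters, and the baseline adjustment in Analyses, which the continuous outcomes need.

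**Conclusion.** The point holds as one of imprecise specification on the sizing outcome. Recovery has no baseline value of its own, so the stated rule does not settle its models; baseline severity may be absent, or admitted according to the data. It would be wrong to infer bias in the recovery comparison or an invalid sample size, since randomisation protects the unadjusted estimate and the size assumes no covariates.

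The effect is modest: about 1 to 7 points of one-sided power and 1 to 8 two-sided if baseline severity explains 5-30% of latent variation, and about 1 point at the low end. These figures rest on assumed prognostic strength and on the 19% and 41% recovery rates. The change is worth making because it costs almost nothing and removes discretion from a primary analysis.

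**What to change.** State in Analyses that, because perceived recovery has no baseline value, its logistic models at 3 and 12 months and its GEE always include the baseline pain rating and baseline Kujala score as continuous covariates, whatever the 10% rule says about other variables. Report the unadjusted result beside the adjusted one. Give the adjusted effect also as a standardised risk difference, since adjusted and unadjusted odds ratios are not on the same scale.

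The cost is one or two sentences, settled before the data are analysed. No new data are needed if, as inferred, both scores are collected at baseline. The statistical price is two extra parameters against about 37 expected recoveries, which is acceptable.

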### Cost-analysis

For the economic evaluation a societal perspective is employed. The relevant costs are divided into direct medical costs and productivity costs.

#### - Direct costs

The costs of health care utilization during the twelve months follow-up consist of visits to a general practitioner, medical specialist, physiotherapist, manual therapist, prescribed and over the counter (OTC) medicines, alternative practitioners and hospitalization and appliances. In the patient questionnaire we ask for the health care consumption in the past six weeks. The costs for the period between two measurements (mostly 3 months) are established through linear interpolation. The medical consumption is valued based on resource costs and guideline costs [15]

#### - Productivity costs

The productivity costs are defined as the costs of absence from work due to PFPS, including the impact of compensation mechanisms [16] the costs of efficiency loss due to PFPS and the costs of hindrance at unpaid work. In the questionnaire the patients are asked to report the reason for absence from work and the number of absent days [17]. To this end we will use the PRODISQ questionnaire [18]. The valuation of an hour work the average productivity costs per hour worked will be based on the Net National Income per working hour[15]. The friction cost method is used to value the productivity costs related to paid work [19]. Productivity costs can also occur when people with health complaints are still working, but at a lower productivity level. This is called efficiency loss. The efficiency losses without absence are established by means of the Quality and Quantity-method [13]. Productivity losses at unpaid work are assessed by hindrance at unpaid work and the number of hours that housekeeping tasks were taken over by other people, and for how many hours paid help was needed. The costs of one hour of housekeeping tasks is set at the current price of one hour of simple professional home care.

#### - Patient outcome analysis in the economic evaluation

The patellar pain may affect Health Related Quality of Life. This is measured with a generic instrument, the EuroQol instrument EQ-5D [20,21] The EQ-5D descriptive system consists of five dimensions (Mobility, Self Care, Usual Activities, Pain/Discomfort and Anxiety/Depression) with three levels each (no problems, some problems and extreme problems), thus defining 243 (35) distinct health states. Respondents of the EuroQol EQ-5D describe their own health using this descriptive system. Preference weights based on the Time Trade-Off method for the 243 EQ-5D health states are available from a large-scale study in the UK[20,21]and a recent Dutch study [22] to calculate EQ-5D index scores that can be used as utilities to calculate QALYs.

## Discussion

The PEX-study has been designed after reviewing the literature on exercise therapy for patellofemoral pain syndrome [7]. It was concluded that though exercise therapy may have a beneficial effect on PFPS the scientific evidence is limited due to small sample size and a small amount of studies including a control group.

Based on available literature our research group expects to discover (beneficial) changes from exercise therapy in perceived recovery, pain severity and functional disability in the PEX study.

The PEX study is a randomized clinical trial where exercise therapy is compared to usual care. The trial started in April 2005 and is expected to finish in June 2007. The first results will be available around December 2007.
